## Abstract

**Background:**

Healthcare for people with somatic and comorbid mental diseases can pose a challenge to the healthcare system. The aim of the SoKo study (the Somatic care of patients with mental Comorbidity) is to assess the current state of care and the facilitators and barriers of somatic care of people with somatic disorders and comorbidity of a mental disorder.

**Methods:**

The study is conducted as a mixed-methods approach and will include (a) descriptive and inferential analysis of secondary claims data of persons insured by a German statutory health insurance company in North Rhine-Westphalia (Techniker Krankenkasse, TK-NRW), (b) qualitative individual interviews and group discussions, and (c) based on (a) and (b), quantitative surveys of both patients and physicians. We intend to analyse a sample of claims data of about 2.6 million persons insured by TK-NRW (group comparisons between TK-NRW insured persons with a diagnosis of a prevalent somatic disease [ICD-10-GM E01–E07, E11, E66, I10–I15, I20–I25, I60–I64] with and without comorbidity of a mental disorder [F00–F99]), in order to assess the uptake of somatic care by people with mental and somatic comorbidity. In addition, primary data from patients with the aforementioned somatic illnesses and a mental comorbidity as well as primary data from physicians (general practitioners and medical specialists) will be collected. The focus here will be on support factors and barriers in the somatic care of people with mental comorbidity.

**Discussion:**

Up to now, there have been no published results of a systematic collection of both secondary and primary data on the utilisation of different care services of somatically ill patients with mental comorbidity for Germany. The present mixed-methods study aims to address this gap.

**Trial registration:**

The trial is registered with the German Clinical Trials Register DRKS: DRKS00030513. The trial was registered on 3rd February 2023.

## Background

Mental disorders are highly prevalent in the general population. In Germany, the 12-month prevalence of mental disorders is about 25–30% of the population [1]. Moreover, comorbidity of mental and somatic diseases is a frequent finding in healthcare data and clinical practice. There are two different ways in which the association of somatic diseases and mental disorders becomes apparent: First, people with somatic disorders have an increased prevalence of comorbid mental illnesses [2, 3]. More specifically, patients with chronic somatic diseases are more likely to develop one of the common mental disorders, such as depression or anxiety disorder, compared to people without somatic diseases [4]. For example, the prevalence of depression is 1.5 to 3 times higher in people with diabetes mellitus [5, 6]. On the other hand, people with several mental illnesses (SMIs), such as depression, bipolar disorder, schizophrenia, and anxiety disorder, have an increased risk of somatic comorbidity [3, 7, 8], especially cardiovascular [3, 9] and metabolic diseases [10]. The increased prevalence of somatic disorders is associated with an increased need for somatic healthcare. For example, the rate of hospitalization for cardiovascular disease is increased by 15% [9]. Somatic-mental comorbidity leads to decreased life expectancy and increased mortality rates [9]. In spite of these adverse health outcomes, studies show that people with SMIs show reduced utilization of healthcare screening and treatment services for somatic diseases such as breast cancer screening in comparison to people without SMIs [11–14]. Furthermore, people with mental disorders tend to receive fewer medical services for cardiovascular disease, diabetes mellitus, and breast cancer than people who are not mentally ill [11, 15]. Furthermore, the comorbidity of mental and somatic illnesses is associated with increased functional limitations, a reduced quality of life, and increased healthcare costs [3, 16]. Especially in SMIs such as schizophrenia, life expectancy is significantly shortened [17]. Potential causes include but are not limited to an unhealthy lifestyle, an accumulation of somatic comorbid diseases, side effects of medication, and inadequate medical care [11, 13, 14, 18, 19]. Taken together, the special healthcare needs of people with comorbid somatic and mental diseases can pose a challenge to the healthcare system [3, 20, 21].

Former studies have focused on the reasons for the increased mortality rates and on the question of how access to health services for people with comorbid mental and somatic disorders can be improved [3, 11–19]. To our knowledge, there are no findings based on the combination of primary and secondary data on the somatic care situation of patients with mental and somatic comorbidity. In the SoKo study (**So**matic care of patients with mental **Co**morbidity), we aim to capture the current uptake of the somatic care of patients with mental comorbidities in Germany and to analyse possible differences of healthcare uptake between the various comorbid mental disorders. Since mental illnesses can be very different in severity and different limitations can accompany them, distinguishing the various manifestations of mental illnesses is indispensable for the analyses. Furthermore, the somatic diseases to be investigated were selected due to their high prevalence, their therapeutic treatability, and their impact in terms of impairments of life expectancy and quality of life. We therefore include diseases of the thyroid gland, arterial hypertension, type 2 diabetes mellitus, obesity, coronary heart disease, stroke, and breast cancer (ICD-10-GM E01–E07, E11, E66, I10–I15, I20–I25, I60–I64). We expect that by choosing these somatic disorders, the implementation of the recommendations for action based on the project results should lead to significant healthcare improvements.

We will analyse statutory health insurance (SHI) claims data of people with mental and the aforementioned somatic diseases to assess healthcare utilization rates in Germany [work package (WP) I]. As little is known about the particular needs of, barriers to, and helpful resources for the somatic care of patients with mental disorders, we will also analyse primary data from interviews/focus groups and questionnaires on the perspectives of both patients (WP II – qualitative data; WP IV – quantitative data) and physicians (WP III – qualitative data; WP V – quantitative data).

By combining results from these different data sources, we aim to develop recommendations to improve access to health services and the quality of healthcare for patients with somatic and comorbid mental illnesses. We anticipate that our research approach will address the following hypotheses:

Primary hypothesis.

The somatic care of patients with mental comorbidity is quantitatively and qualitatively different to the somatic care of patients without mental comorbidity.

Secondary hypotheses.

2.Mental and somatic multimorbidity is a barrier to the somatic care of people with mental illnesses.3.Certain SMIs, such as schizophrenia, are more often a barrier to somatic care than other mental illnesses.4.Transitional barriers at the interfaces between in Germany traditionally segregated inpatient and outpatient care sectors represent a barrier to the provision of care.5.Good health literacy is beneficial for the somatic care of patients with mental comorbidity.6.Good social integration has a positive correlation with somatic care of patients with mental comorbidity.7.Characteristics of the treating physicians (professional experience, prejudices) can be associated with the somatic care of patients with mental comorbidity.

The primary hypothesis as well as the secondary hypotheses 2–4 will be investigated by analysing the claims data of persons insured with the TK-NRW (WP I). The primary data from interviews and questionnaires is expected to provide relevant content and constructs for the secondary hypotheses 4–7 (WP II – V).

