## Methods/design

This study is performed by the LVR-Institute of Healthcare Research (LVR-IVF) in cooperation with the LVR-Clinic Düsseldorf and the Techniker Krankenkasse North Rhine-Westphalia, division of a German Statutory Health Insurance Company (TK-NRW).

The SoKo study includes persons who have already made use of the healthcare system due to common somatic diseases (thyroid gland, arterial hypertension, type 2 diabetes mellitus, obesity, coronary heart disease, stroke, and breast cancer (ICD-10-GM E01–E07, E11, E66, I10–I15, I20–I25, I60–I64, C50)). These somatic diseases include both acute and chronic conditions, which require different types of outpatient, inpatient and rehabilitative care. We will study the somatic care of persons who suffer from at least one of these somatic diseases and compare it to the care of persons who suffer from at least one of these somatic diseases and are also diagnosed with a mental disorder (ICD-10-GM F00–F99). All participants are insured with TK-NRW. TK-NRW will provide anonymised claims data of all members who are diagnosed with at least one of the aforementioned somatic disorders. We will compare the data of persons without a mental disorder and persons who are diagnosed with at least one of the aforementioned somatic disorders and a mental disorder (WP I). In addition, TK-NRW will invite a number of members who are diagnosed with at least one of the aforementionfed somatic illnesses and a mental disorder to participate in the guideline-based interviews and the survey study (WP II and IV). Moreover, we will conduct guideline-based interviews, focus groups, and a survey among general practitioners (GPs) and medical specialists in internal medicine, psychiatry, psychotherapy, and psychosomatics (WP III and V).

The following inclusion criteria will be applied:

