### Work package I: claims data of persons with and without mental illnesses

The insured persons’ data are anonymized by TK-NRW and are made available to the LVR-IVF for the analyses.

Claims data of persons with at least one of the following common somatic diagnoses (only confirmed diagnoses, ICD-10 code (German Modification)): thyroid disease (E01–E07), obesity (E66), chronic ischaemic heart disease (I25), arterial hypertension (I10–I15), type 2 diabetes mellitus (E11), stroke (I60–I64), or breast cancer (C50) *and no diagnosis of a mental disorder* (F00–F99)).Billing data of patients with at least one of the aforementioned common somatic diagnoses *and* concurrent healthcare service use (documented in the same billing quarter) due to a *confirmed diagnosis of a mental disorder* (F00–F99).

The number of persons insured with TK-NRW amounts to 2.6 million. According to the Robert Koch-Institute (2017), the prevalence of hypertension in Germany is 30.9% in women and 32.8% in men [22]. According to the Association of Statutory Health Insurance Physicians in the Federal Republic of Germany, insured persons with arterial hypertension according to ICD-10 were the most frequent cases of treatment in medical practices in the North Rhine region in 2021, at 34.1% [23]. We therefore also assume that arterial hypertension is the most common somatic disease among persons insured with TK-NRW, according to the somatic inclusion criteria mentioned above. Based on data for 2015, we estimated in the project proposal that approximately (approx.) at least 40% (n = 1,040,000) of persons insured with TK-NRW have a somatic disease according to the abovementioned inclusion criteria. TK-NRW estimates that 12–15% of the persons insured with TK have a psychiatric diagnosis that requires inpatient or outpatient treatment. Consequently, we estimate that at least 10% of patients who meet the inclusion criteria of the abovementioned somatic diagnosis groups also have a mental disorder (n = 104,000).

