The power calculations show that with group sizes of n_1_ = 936,000 (secondary data of persons insured by TK-NRW with somatic diseases according to the inclusion criteria described above and without comorbidity of a mental disorder) and n_2_ = 104,000 (secondary data of persons insured by TK with somatic diseases according to the inclusion criteria described above and with comorbidity of a mental disorder), a power of 90%, an alpha of 0.05, and a sensitivity of |d| = 0.01 (Cohen’s d = 0.01) can be achieved.

Inferential statistical procedures such as T-tests, chi-square tests, and further statistical procedures will be used to compare the groups. In particular, differences between the groups of insured persons with somatic and mental illnesses compared to the group of persons with somatic illnesses only, as well as differences between the subgroups of insured persons with different mental illnesses, will be examined. Regression analyses with clinical and socio-demographic co-factors are planned in order to examine outcomes such as cumulative length of stay in inpatient psychiatric treatment, cross-disciplinary care, diagnostic/therapeutic services, therapy density, and mortality. Based on these analyses, associations between healthcare utilization (e.g. utilization rates of psychiatric-psychotherapeutic and somatic care specialists) and outcomes (e.g. Frequency of disability, rates of retirement due to reduced earning capacity, mortality rates) will be analysed. Statistical tests are performed using the Statistical Package for the Social Sciences (SPSS).

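### The primary hypothesis claims a qualitative difference in somatic care, but the named WP I outcomes do not operationalise quality for any index disease, and unadjusted tests over seven pooled diseases may mix disease composition with care

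*Protocol article*

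**What the plan says.** The Background of the protocol article states the primary hypothesis as "The somatic care of patients with mental comorbidity is quantitatively and qualitatively different to the somatic care of patients without mental comorbidity". It then allocates the work: "The primary hypothesis as well as the secondary hypotheses 2–4 will be investigated by analysing the claims data". The interviews and surveys (WP II to V) are allocated to secondary hypotheses 4 to 7. The same section describes the purpose of the claims analysis as assessing utilisation rates, and the Abstract describes it as assessing uptake.

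The WP I section plans regressions with clinical and socio-demographic co-factors for "outcomes such as cumulative length of stay in inpatient psychiatric treatment, cross-disciplinary care, diagnostic/therapeutic services, therapy density, and mortality". It adds associations between utilisation and outcomes, with these examples: "Frequency of disability, rates of retirement due to reduced earning capacity, mortality rates". Groups are compared by t-tests, chi-square tests and unspecified further procedures.

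The population is defined by "Claims data of persons with at least one of the following common somatic diagnoses", followed by seven disease groups: thyroid disease, obesity, chronic ischaemic heart disease, hypertension, type 2 diabetes, stroke and breast cancer. Of these diseases the Methods/design section says: "These somatic diseases include both acute and chronic conditions, which require different types of outpatient, inpatient and rehabilitative care". The only subgroups named for comparison are mental disorders.

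**The concern.** There are two gaps between the hypothesis and the measures.

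First, the qualitative half of the primary hypothesis rests on claims data alone, yet no named outcome is presented as a measure of the quality of somatic care. A count of services or a density of therapy could be higher because care is better, because patients are sicker, or because earlier treatment failed. The study intends to derive recommendations for improving quality of care, and these need a measure that says which way is better.

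Second, the two groups pool diseases with different care needs. If the disease mix differs between persons with and without a mental disorder, an unadjusted comparison can show a difference even when care within every disease is the same. With about a million persons, a very small shift in mix is enough.

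**Working it through.** **Step 1: hypothesis against outcomes.**

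| Named WP I outcome | What it captures |
|---|---|
| Cumulative inpatient psychiatric stay | Psychiatric, not somatic, care; should be almost absent in a comparator defined by having no F00–F99 diagnosis |
| Cross-disciplinary care, diagnostic/therapeutic services | Kind and amount of care; not linked to what a given disease requires |
| Therapy density | Amount of care |
| Mortality, disability, early retirement | Health or social end results with a clear adverse direction, but not attributes of the care given |

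No other package closes the gap. WP II and IV recruit only insured persons who have both a somatic and a mental diagnosis, so they have no comparison group. WP III and V address physicians.

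**Step 2: reproduce the stated sensitivity.** Inputs from the WP I section: n1 = 936,000, n2 = 104,000, power 90%, alpha 0.05, |d| = 0.01. Sidedness is not stated.

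- Group sizes: 2,600,000 × 0.40 = 1,040,000; × 0.10 = 104,000; remainder 936,000. These agree.
- Standard error of d: √(1/936,000 + 1/104,000) = 0.00327.
- Detectable d, two-sided: (1.960 + 1.282) × 0.00327 = 0.0106. One-sided: (1.645 + 1.282) × 0.00327 = 0.0096.

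Both round to the stated 0.01, so the figure is reproduced to two decimals. At exactly d = 0.0100, power is 86.4% two-sided.

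**Step 3: how much disease mix is enough?** Suppose care within each disease is identical in both groups. Let two disease types differ in mean outcome by Δ (in SD), and let the share of one type differ between the groups by s. The unadjusted comparison then shows

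d = Δ × s.

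The documents give neither Δ nor s; both are assumed here over a range. The shift that produces d = 0.01 is s = 0.01/Δ:

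| Assumed Δ (SD) | Shift giving d = 0.01 |
|---|---|
| 0.1 | 10 points |
| 0.2 | 5 points |
| 0.5 | 2 points |
| 0.8 | 1.25 points |

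Chance that an unadjusted two-sided test is significant from mix alone:

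| Assumed Δ | Assumed shift | d | Chance |
|---|---|---|---|
| 0.2 SD | 2 points | 0.004 | 23% |
| 0.2 SD | 5 points | 0.010 | 86% |
| 0.5 SD | 2 points | 0.010 | 86% |
| 0.5 SD | 5 points | 0.025 | over 99.9% |

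These figures apply to a comparison that does not account for index disease. They do not apply to a regression that includes it.

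**The case against.** The other side has several good arguments.

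- The outcome and test lists are introduced as examples, and an article condenses the full protocol. A reader might infer that the quality half cannot be answered at all. The text does not support that: cross-disciplinary care and diagnostic/therapeutic services could be developed into disease-specific indicators. What stands is that this document does not do so, although it fixes the hypothesis and its data source and describes WP I as an analysis of utilisation.
- The hypothesis says only that care differs, and a difference can be tested without a direction. This stands. The missing direction limits the interpretation of a difference, not its detection. *Qualitatively* could also mean different in kind, but the article elsewhere names quality of care as something to be improved.
- Regressions with clinical co-factors are planned for these same outcomes, and secondary hypothesis 2, on multimorbidity, suggests that somatic diagnoses will be available as variables. The mix risk is therefore established only for the unadjusted tests. It applies to the regressions only if index disease is left out, which the text does not settle.
- A reader might infer from the Background, which reports more cardiovascular and metabolic disease in people with mental illness, that the mix will differ. That statement concerns people with mental illness in general, whereas everyone in WP I already has an index disease. It supports only that the mix may differ.
- A reader might also fear that many contacts would be counted as good care. Nothing in the plan scores them that way.

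**Conclusion.** The point holds in a limited form. The primary hypothesis includes a claim about the qualitative side of somatic care, it is assigned to WP I alone, and none of the named outcomes operationalises quality for any index disease. A difference in them would support a statement about utilisation or end results, not about better or worse care.

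The pooled t-tests and chi-square tests may also mix disease composition with care. Under assumed outcome differences of 0.8 down to 0.1 SD between disease types, a shift in mix of about 1 to 10 points equals the effect the study is sized to detect. Those differences and shifts are assumptions, and whether any shift exists is unknown from the document. Effects of this size are small in absolute terms; they matter because the plan is sized to call them significant. The documents do not support the stronger conclusion that the primary comparison as a whole is confounded, since the regressions may adjust for index disease.

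**What to change.** In WP I:

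1. Report the comparison between persons with and without a mental disorder within each index disease. Give a pooled figure only after adjusting for index disease or standardising to a common index-disease distribution, and name index disease among the clinical co-factors.
2. For the quality half, set in advance one or two billed process indicators per disease with a stated direction: for example, the share of eligible persons with that disease who had a named monitoring, dispensing or follow-up service billed within a set number of quarters. Do this as far as the TK-NRW extract contains the variables.
3. Keep service volumes as the quantitative half.
4. If the extract does not support such indicators, delete *and qualitatively* from the primary hypothesis and limit the conclusion to utilisation.

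The article places data delivery in the second quarter of 2023 and plausibility checks in the third and fourth, so on that timetable the indicators can be chosen before analysis.

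The cost is a short indicator list, more tables, and several disease-specific results beside the pooled one, each restricted to eligible persons. The second item depends on what the extract delivers. The article does not list its contents and reports that extraction was already difficult. The fourth item is a wording change only.

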## Methods/design

This study is performed by the LVR-Institute of Healthcare Research (LVR-IVF) in cooperation with the LVR-Clinic Düsseldorf and the Techniker Krankenkasse North Rhine-Westphalia, division of a German Statutory Health Insurance Company (TK-NRW).

The SoKo study includes persons who have already made use of the healthcare system due to common somatic diseases (thyroid gland, arterial hypertension, type 2 diabetes mellitus, obesity, coronary heart disease, stroke, and breast cancer (ICD-10-GM E01–E07, E11, E66, I10–I15, I20–I25, I60–I64, C50)). These somatic diseases include both acute and chronic conditions, which require different types of outpatient, inpatient and rehabilitative care. We will study the somatic care of persons who suffer from at least one of these somatic diseases and compare it to the care of persons who suffer from at least one of these somatic diseases and are also diagnosed with a mental disorder (ICD-10-GM F00–F99). All participants are insured with TK-NRW. TK-NRW will provide anonymised claims data of all members who are diagnosed with at least one of the aforementioned somatic disorders. We will compare the data of persons without a mental disorder and persons who are diagnosed with at least one of the aforementioned somatic disorders and a mental disorder (WP I). In addition, TK-NRW will invite a number of members who are diagnosed with at least one of the aforementionfed somatic illnesses and a mental disorder to participate in the guideline-based interviews and the survey study (WP II and IV). Moreover, we will conduct guideline-based interviews, focus groups, and a survey among general practitioners (GPs) and medical specialists in internal medicine, psychiatry, psychotherapy, and psychosomatics (WP III and V).

The following inclusion criteria will be applied:

